### Eligibility Criteria

We will prospectively and consecutively recruit adult patients aged 18 to 75 years who present either with acute cough as the predominant symptom—considered by the GP to be a bacterial acute lower RTI, as defined by the European Society for Clinical Microbiology and Infectious Diseases [32]—or with clinically suspected acute bacterial rhinosinusitis, as defined by the American Academy of Otolaryngology–Head and Neck Surgery Foundation [33], in cases where the GP considers a standard β-lactam course to be necessary. Patients who meet criteria for hospital referral, have a known allergy to β-lactams, are immunocompromised, or are in a severe clinical condition will be excluded from the study. A detailed summary of all inclusion and exclusion criteria is provided in Textbox 1. All patients who agree to participate will provide a signed informed consent and will be informed about the nature of this study. The participating GPs will prescribe an antibiotic, and the patient will be later randomized. Patients in the intervention group will be asked to return to the center as soon as they feel better and are afebrile for an assessment of the clinical stability criteria and CRP measurement.

Eligibility criteria.
**Inclusion criteria (all the criteria must be met):**
Age ranging from 18 to 75 years.Either acute lower respiratory tract infection (RTI) or bacterial rhinosinusitis.Acute lower RTI: acute cough (new or worsening of a previous cough present for 21 days or less) as the predominant symptom, accompanied by at least one other lower respiratory tract symptom—such as sputum production, dyspnea, wheezing, and chest discomfort/pain—with no alternative explanation. It is presumed to have a bacterial cause, such as community-acquired pneumonia, acute bronchitis, or acute exacerbations of chronic obstructive pulmonary disease (COPD), according to the clinician’s judgment.Acute bacterial rhinosinusitis: presence of purulent nasal discharge or facial pain/pressure lasting less than 4 weeks, which the clinician suspects to be bacterial due to lack of improvement within 10 days, severe symptoms from day 3, or worsening after day 5.General practitioners deem β-lactam therapy for at least 7 days is necessary.
**Exclusion criteria (any of the following exclusion criteria):**
RTIs different from a lower RTI or acute rhinosinusitis.The doctor decides not to give an antibiotic for this RTI.Patients with suspected septicemia (quick sequential organ failure assessment: respiratory rate ≥22 breaths/minute, systolic blood pressure <100 mm Hg, or altered mental status with a Glasgow score < 5) ≥2.Patients with pneumonia and a CRB-65 (confusion, respiratory rate ≥30 breaths/minute, blood pressure < 90/60 mm Hg, or age >65 years) ≥1.Patients with very severe COPD (forced expiratory volume in 1 second [FEV_1_]<30%).Patients with COPD who have taken 4 or more antibiotic courses in the previous year, the presence of significant bronchiectasis, and isolation of Pseudomonas in a previous sputum culture.Patients with reported allergy to β-lactams.Patients who have taken antibiotics in the previous 2 weeks.A working diagnosis of a noninfective disorder, such as heart failure, pulmonary embolus, or esophageal reflux.Immunocompromised patients, such as those with HIV infection, patients taking immunosuppressive treatment, antineoplastic therapy, or systemic corticosteroids.Currently participating in another clinical trial.Previously participated in the STORM study.Active neoplasia.Terminal illness.Institutionalized patient.Inability/unable to understand or take part in the clinical trial.

GPs will be informed about managing acute RTIs with β-lactam therapy, following the specific RTIs outlined in this study and the latest Spanish primary care guidelines [34,35] (Table 1). The guidelines recommend the use of 7-day antibiotic durations. Doctors participating in this study will be provided with a summary of the current local guidelines, including indications for when to treat. However, the final decision on antibiotic prescriptions will be at the discretion of the GP. The trial is pragmatic, aiming to mirror the real-life practices of doctors in Spain. According to a recent study conducted in Barcelona in 2023, approximately 80% of all prescriptions for amoxicillin and amoxicillin-clavulanate in primary care corresponded to box sizes of 30 pills, representing a 10-day duration, while the remainder were 20-pill boxes [36]. Considering that this clinical trial is pragmatic, we will consider a minimal duration of 7 days.

**Table 1 table1:** Guidelines for prescribing antibiotics for respiratory tract infections in primary care in non-β-lactam-allergic patients in Spain, based on the updated recommendation [34,35] (to be performed by the general practitioner).

Diagnosis	When is it appropriate to prescribe antibiotics?	First choice antibiotic
Acute rhinosinusitis^a^	Do not administer, unless there are signs and symptoms that do not improve within 10 days, severe symptoms from day 3, or worsening of symptoms from day 5	Amoxicillin and clavulanate 875-125 mg/8 h/7 d or penicillin V 1000 mg/8 h/7 d
Lower respiratory tract infection (non-COPD^b^)^c^	In acute bronchitis, antibiotics should not be given, except in specific situations. Always treat in pneumonia	Amoxicillin 1000 mg/8 h/7 d or penicillin V 1.000 mg/8 h/7 d. Amoxicillin and clavulanate 875-125 mg/8 h/7 d if age >65 years
COPD exacerbation^d^	Only if there is sputum purulence and in all very severe or very severe COPD exacerbations	Amoxicillin and clavulanate 875-125 mg/8 h/7 d

^a^Refer to the hospital if persistent temperature >39 °C, periorbital oedema, intense headache, neurological focal signs, signs of meningeal irritation, impaired consciousness, suspicion of orbital infection, or diplopia.

^b^COPD: chronic obstructive pulmonary disease.

^c^Refer to the hospital if oxygen saturation <92%, significant alterations in chest x-ray, difficulties in complying with treatment at home, decompensation of underlying illness, lack of tolerance to oral treatment, immunosuppression, or CRB65 ≥1. Refer to the hospital if CRB65 >1 (confusion, respiratory rate ≥30 breaths/min, systolic blood pressure <90 mm Hg or diastolic blood pressure <60 mm Hg, age >65 years.

^d^Impaired consciousness, cyanosis, respiratory rate ≥30 breaths/min, severe dyspnea, oxygen therapy, inability to stay at home, or oxygen saturation <92%. Patients with COPD with forced expiratory volume in 1 second (FEV_1_) <30% are excluded from this study.

Eligible participants will be informed about the STORM trial and provided with an information leaflet and a consent form from the GP. The GP will ensure that the patient understands the purpose of the project, potential benefits, risks, and procedures involved. The GP will emphasize that participation is voluntary and that the patient can decline to participate or withdraw from the project at any time without consequences. The patient is informed that consent to participate will give the primary investigator, sponsor, and controlling authorities access to obtain information in the patient’s medical records, including the electronic records, to obtain information about the patient’s health conditions. The GP will check patients against the eligibility criteria stated above and invite patients to participate if they fulfill all the inclusion criteria and none of the exclusion criteria. Patients who agree to participate will be asked to provide written consent, which will be obtained by the GP. Informed consent will be obtained prior to the collection of participant data. Participants will be informed about the storage and use of their data.

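### The septicemia exclusion counts altered mental status only at a Glasgow score below 5, so that item cannot score in anyone who could otherwise be enrolled

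*Protocol article*

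**What the plan says.** In the protocol article, the exclusion criteria (Textbox 1) remove patients with suspected septicemia, using the quick sequential organ failure assessment with exclusion at a score of 2 or more. The three items are respiratory rate ≥22 breaths/minute, systolic pressure <100 mm Hg, and "altered mental status with a Glasgow score < 5". No other part of the text shown gives a Glasgow cut-off.

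Several other rules touch the same patients:

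- **Eligibility Criteria, main text.** Two groups are kept out: "Patients who meet criteria for hospital referral" and those who "are in a severe clinical condition will be excluded from the study".
- **Exclusion criteria, pneumonia.** "Patients with pneumonia and a CRB-65 (confusion, respiratory rate ≥30 breaths/minute", low blood pressure or age over 65 is excluded at a score of 1 or more.
- **Exclusion criteria, capacity.** "Inability/unable to understand or take part in the clinical trial" is a separate exclusion.
- **Table 1, note a (rhinosinusitis).** The hospital referral list includes "signs of meningeal irritation, impaired consciousness, suspicion of orbital infection, or diplopia".
- **Table 1, note c (non-COPD lower RTI).** Referral follows "lack of tolerance to oral treatment, immunosuppression, or CRB65 ≥1", and also "significant alterations in chest x-ray, difficulties in complying with treatment at home". The next sentence of the same note sets referral at CRB65 >1.
- **Table 1, note d (COPD exacerbation).** Impaired consciousness is listed, without a verb saying that it triggers referral.
- **Consent text after Table 1.** The GP must make sure that the patient understands the study, and obtains written consent.

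**The concern.** The label and the number of the third item disagree. Altered mental status is a broad sign that includes drowsiness and confusion, whereas a Glasgow score below 5 describes a comatose patient. Such a patient would never be considered for an outpatient trial that requires understanding and a signature, so the item adds nothing to the screen.

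This is a decision threshold that GPs are told to apply before enrolling someone in a trial of earlier antibiotic stopping. The Discussion (Principal Findings) also relies on potentially serious infections having been excluded. At stake is whether a mildly altered patient with one further warning sign could pass the criterion meant to catch early sepsis.

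**Working it through.** The printed cut-off is a stated threshold and not a derived number, so there is no calculation of the plan's to reproduce. The check has three steps.

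**1. What a score below 5 means.** Assume the usual scale: eye 1–4, verbal 1–5, motor 1–6, total 3–15. A total below 5 is 3 or 4, and the only combinations are 1-1-1, 1-1-2, 1-2-1 and 2-1-1. A fully oriented verbal response alone gives at least 1 + 5 + 1 = 7. Eyes open spontaneously and obeying commands gives at least 4 + 1 + 6 = 11. No one able to follow a consent discussion can score below 5.

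**2. What is left of the two-of-three rule.** Three items form 3 pairs. Only 1 pair (respiratory rate ≥22 with systolic <100) does not use the mental-status item, so only that pair can reach 2. For example, a patient with Glasgow 14, rate ≥22 and systolic ≥100 scores 1 + 0 + 0 = 1 as printed and is not excluded. If any score below 15 counted, the same patient would score 1 + 0 + 1 = 2 and be excluded.

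**3. How much of the gap CRB65 covers.** Take an altered patient, drowsy or confused, and cross this with:

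- respiratory rate (<22, 22–29, ≥30)
- systolic pressure (≥100, 90–99, <90)
- age (18–65, 66–75)

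This gives 2 × 3 × 3 × 2 = 36 profiles. A corrected item changes the decision only where exactly one of the other two signs is present. That is 4 rate/pressure combinations × 2 ages × 2 mental states = 16 profiles. The CRB65 score is confusion + (rate ≥30) + (systolic <90) + (age >65), with diastolic taken as ≥60 when systolic is ≥90:

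| Rate; systolic | Drowsy 18–65 | Drowsy 66–75 | Confused 18–65 | Confused 66–75 |
|---|---|---|---|---|
| <22; 90–99 | 0 | 1 | 1 | 2 |
| <22; <90 | 1 | 2 | 2 | 3 |
| 22–29; ≥100 | 0 | 1 | 1 | 2 |
| ≥30; ≥100 | 1 | 2 | 2 | 3 |

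- **Referral at CRB65 ≥1:** the uncovered cells are those equal to 0, so 2 of 16, both drowsy.
- **Referral at CRB65 >1:** the uncovered cells are those equal to 0 or 1, so 4 + 2 + 2 + 0 = 8 of 16 (6 drowsy, 2 confused).

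By diagnosis:

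- **Rhinosinusitis:** note a lists impaired consciousness, so 0 of 16 remain.
- **COPD exacerbation:** 0 of 16, if note d is read as a referral list.
- **Pneumonia:** the exclusion criterion itself uses ≥1, so 2 of 16 remain, and the chest x-ray referral in note c may remove some of these.
- **Other lower RTI:** 2 or 8 of 16, according to which sentence of note c the GP applies.

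All counts are before the understanding, consent and severe-condition rules.

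**The case against.** The strongest reply is that the error has almost no consequence. To slip through, a patient must be mildly altered, show exactly one of the two vital signs, miss the referral and severe-condition exclusions, satisfy the GP that the study is understood, sign, and be judged fit for oral treatment at home. The criterion is also labelled as suspected septicemia and names its instrument, so a GP is not guided by the Glasgow figure alone. And an exclusion criterion is applied before consent, so it need not be one that a consenting patient could meet. All of this stands as an argument for low severity. It does not rescue the number, because an item that singles out only patients already barred by other rules does no work.

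A second reply is that the replacement value comes from outside the documents, and that Figure 1, the full protocol and the e-CRF are not shown. This also stands in part. The defect needs only the range of the scale, but a cut-off of <15 has to be confirmed against the named instrument. A digit lost in text extraction cannot be excluded either, although nothing in the text points to it.

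Two stronger readings are tempting. A reader might infer that septic patients will be enrolled. The overlapping rules do not support that. A reader might equally infer that the overlap leaves at most 2 of 16 profiles and catches every confused patient. That holds only for the ≥1 sentence of note c and fails under the >1 sentence beside it. The profiles are also unweighted, and the split into drowsy and confused is a device of this check, so neither count says how many patients are involved.

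**Conclusion.** The printed cut-off is wrong for its purpose. It disables one of the three items and reduces the rule to respiratory rate ≥22 with systolic pressure <100. The conclusion assumes the ordinary 3 to 15 scale. That the figure is a slip, and not a choice, is an inference from the mismatch between label and number.

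The practical effect is small. Other rules cover much of the gap and few patients should be affected. For lower RTI that is neither pneumonia nor COPD, no upper bound on the uncovered profiles should be claimed, because note c contradicts itself. Sample size, power and analysis do not depend on this threshold. It is an optional correction (COULD), justified because it concerns a safety exclusion and costs very little.

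**What to change.** In the septicemia exclusion, replace the Glasgow cut-off with any altered mental status, that is, a score below the maximum of 15, after confirming this against the quick sequential organ failure assessment that the criterion names. Check that Figure 1 and the e-CRF screening form do not carry the <5 figure.

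The cost is a one-figure text correction and a check of two items, with no change to sample size or analysis.

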### Interventions

Patients assigned to usual care will be given a full course of the first-line antibiotic course as recommended by the updated local guidelines [34,35]: amoxicillin 750 mg 3 times daily (t.i.d.) for 7 days for acute rhinosinusitis, 1000 mg t.i.d. for 7 days for suspected pneumonia (with clavulanate if the patient is older than 65 years), and amoxicillin/clavulanate 875 mg/125 mg t.i.d. for 7 days for suspected acute exacerbations of COPD (Table 1). Nonetheless, this guideline is designed to serve as a reference for making informed and improved choices in prescribing. The decision to prescribe an antibiotic is solely at the discretion of the participating doctor. The trial is pragmatic, thus mirroring the real-life practices of doctors in Spain. Doctors may also prescribe antibiotics for longer regimens, such as 10-day durations, as shown in recent studies [36]. The decision to prescribe an antibiotic will always be made before randomizing the patient.

Patients in the intervention group will be treated accordingly, following the same recommendations as patients assigned to the control group, but they will be asked to return as soon as they feel better and are afebrile.

When deciding whether to discontinue the antibiotic course after a patient feels better during a consultation, the participating professionals must assess three key areas:

Overall improvement in the patient’s symptoms.Evaluate the vital signs, confirming that most of them are within the normal range and that the following clinical criteria are met: temperature <37 °C, blood pressure >90/60 mm Hg, pulse <100 beats/min, respiratory rate <20 breaths/min, and oxygen saturation >92%.Assess the CRP value and interpret the results according to the provided table based on current recommendations [37].

Patients who meet all these criteria will be asked to discontinue treatment. Otherwise, patients will be instructed to continue the course for 2 more days and, if they continue feeling better, to return for reassessment. In case of worsening symptoms, they will be advised to contact their doctor for clinical assessment. The doctor will then decide whether to recommend completing the full antibiotic course, changing the therapy, or making a referral.

### Criteria for Discontinuing or Modifying Allocated Interventions

Due to the short intervention period after index consultation, the allocated intervention may only be discontinued for a given trial participant by the GP due to an unexpected event, hindering the GP from conducting or completing the allocated intervention, for example, acute worsening of the participant’s condition during index consultation, after consent has been given and allocation has been revealed. Moreover, the study may be discontinued for a given trial participant upon participant request or by withdrawal of informed consent. The data collected before the discontinuation or withdrawal of consent will be retained and used in the analyses; however, no further data will be obtained from the participant.

### Strategies to Improve Adherence to Interventions

Monthly meetings with the coordinators of the different centers will be carried out during the performance of the randomized clinical trial. Each center will have a centralized mobile phone for the study, through which patients will contact when they feel well to be directly scheduled at the center as soon as possible to assess the discontinuation of the antibiotic.

### Relevant Concomitant Care Permitted or Prohibited During the Trial

Treatments taken on a chronic basis will be permitted, such as inhaled corticosteroids, beta-agonists, anticholinergics, symptomatic treatments, and medications for other concomitant diagnoses, as all these treatments must be distributed evenly between the 2 groups. Patients taking immunosuppressive treatment, antineoplastic therapy, systemic corticosteroids, or antibiotics in the previous 2 weeks will be excluded.

### Outcomes

#### Primary Efficacy Endpoint

The primary outcome is the percentage of patients achieving clinical resolution, defined as the disappearance of fever and either the disappearance or improvement in overall condition, such that no additional antimicrobial treatment is necessary. Any other clinical outcome that does not meet the definition is considered treatment failure. The evaluation will take place on day 14 via a phone call and will always be conducted by a doctor from the team of physicians participating in the study.

#### Secondary Efficacy Endpoints

##### Outcomes Collected From the RTI Symptom Diaries

Participants will use a validated self-reported RTI symptom diary, used in previous studies by the research team [40]. Each symptom will be graded on a 7-point Likert scale (0=not affected; 1=very little problem; 2=slight problem; 3=moderately bad; 4=bad; 5=very bad; 6=as bad as it could be). Symptoms recorded include cough, phlegm, shortness of breath, wheeze, blocked/runny nose, facial pain, chest pain, sensation of fever (high temperature), muscle aching, headache, disturbed sleep, feeling generally unwell, and interference with normal activities/work. Participants will rate symptoms for 14 days and return the diary upon completion (electronically or paper-based). It will document daily antibiotic doses and other therapies. For patients who do not return diaries, a short form asking about how many days antibiotics were actually taken, whether antibiotics have been taken after being discontinued by their doctors, and details of the duration and severity of symptoms will be completed by a telephone call to the patient at day 14.

Duration of antibiotic therapy, in days, defined as the number of days until discontinuing treatment in both groups (mean/median)Use of antibiotics other than the study medication and other symptomatic therapies within the first 2 weeks (mean/median)Early clinical assessment based on the overall score at Day 7, defined as the total symptom score reported by the patient on that day (mean/median)Duration of severe symptoms, in days, defined as the number of days until the last day the patient scores 5 in any of the symptoms (mean/median)Duration of moderate symptoms, in days, defined as the number of days until the last day the patient scores 3 in any of the symptoms (mean/median)Total resolution of symptoms, in days, defined as the number of days until the last day the patient scores 0 in all the symptoms (mean/median)The duration of antibiotic therapy, in days, defined as the number of patients discontinuing treatment in both groups, and day they discontinue will also be checked via electronic medical records

Outcomes 1 to 7 from the RTI symptom diary will be calculated for each participant every day from day 0 until day 14 or when the participant has scored 0 for every item, whichever comes first.

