### Objectives

The primary aim of the STORM trial is to assess whether the clinical resolution on day 14 for adults presenting with symptoms of an acute lower RTI or acute rhinosinusitis in general practice is noninferior in the intervention group (stopping the antibiotic course as soon as patients feel better and clinical assessment is within the normal range) compared with the control group (patients completing standard antibiotic courses).

Secondary objectives of this trial are as follows:

Evaluate the antibiotic prescribed at the index visit and the planned and actual duration in the 2 groups.Evaluate the adherence to the prescribed antibiotic in the 2 groups.Evaluate the early clinical resolution on day 7.Evaluate the duration of symptoms in the 2 groups: (1) duration of severe symptoms, (2) duration of moderate symptoms, and (3) total resolution of symptoms.Evaluate the use of antibiotics other than the study medication and other symptomatic therapies within the first 4 weeks in the 2 groups.Determine the number of reattendances to any doctor regarding the infection within the first 4 weeks in the 2 groups.Determine the number of complications related to the infection within the first 4 weeks, such as visits to emergency departments, hospital admissions, in the 2 groups.Determine the number of adverse events in the 2 groups.Estimate the incremental cost per patient achieving clinical resolution (within-trial cost-effectiveness analysis) and the incremental cost per quality-adjusted life year (long-term cost-effectiveness analysis) in the 2 groups.Determine the number of days of work absenteeism due to the infectious disease in the 2 groups.Determine the improvement in health-related quality of life in the 2 groups.Assess the percentage of patients assigned to the intervention group who feel better and who comply with the criteria for stopping the antibiotic therapy in the 2 groups.

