##### Outcomes Collected From Electronic Case Report Forms, When Available, and From Follow-Up Phone Calls, Which Will Be Cross-Checked With the Patients’ Electronic Clinical Records

Type of antibiotic prescribed and the planned duration.Number of reattendances to any doctor for new or worsening symptoms regarding the infection, within 28 days after the index consultation.Number of complications related to the infection within 28 days after the index consultation, such as visits to emergency departments or hospital admissions regarding the RTI.Number of days of work absenteeism due to the infectious disease, within 28 days after the index consultation.Difference in health-related quality of life on days 14 and 28, compared with baseline, measured using the 5-level EQ-5D version-quality of Life instrument (ie, EQ-5D-5L) [41].Drug-associated adverse events related to the antibiotic, defined as any harmful and unintended health incident—such as a symptom, an abnormal laboratory finding, or worsening of a pre-existing condition—temporally associated with the use of the antibiotic, regardless of whether it is causally related to the treatment, and antibiotics changed within the first 14 days.

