Day 0 (inclusion date at the center): Patients meeting the inclusion criteria will be invited to join the study by their GP. After obtaining informed consent, patients will be randomized into either the control group (receiving a full course of β-lactam therapy for at least 7 days) or the intervention group (instructed to return for assessment upon feeling better and being afebrile). The GPs will complete a case report form on day 0 (inclusion day), recording details such as age, inclusion and exclusion criteria, symptoms, date of symptom onset, comorbidities, concomitant medication, quality-of-life questionnaire (EQ-5D-5L instrument), randomization, assigned group, and details of the antibiotic administered. Patients will also be provided with a symptom diary (web-based or paper-based)From day 1 until the last day of the antibiotic regimen duration (at the center, only for patients assigned to the intervention group): For patients assigned to the intervention, they will be asked to return to the center for clinical reassessment and CRP rapid testing by the professional. Each center will organize ways to make it easy for patients to reach out and schedule an appointment as soon as they feel better (eg, phone number and web-based page). To decide whether to discontinue the antibiotic course when the patient reports feeling better during the consultation, three types of assessment are needed: (1) overall improvement in the patient’s symptoms; (2) signal signs are in normal range (temperature <37 °C; blood pressure >90/60 mm Hg; pulse < 100 beats/minute; respiratory rate <20 breaths/minute, and oxygen saturation >92%), and (3) CRP value is lower than the prespecified values depending on the day of the visit. All this information will be recorded in the electronic case report form (e-CRF; Table 1)Day 3±1 (phone call, only for patients assigned to the intervention group): A reminder phone call for all patients assigned to the intervention group will be made on this day. They will be asked how they feel and reminded to reach out to the center as soon as they feel better for a discontinuation assessmentDay 7 (phone call): An early clinical efficacy outcome will be assessed during this call, including the clinical progression of signs and symptoms, treatment adherence, adverse reactions, any complications, reattendance visits, changes to the assigned treatment or concomitant medication, and the use of antibiotics other than the study drugDay 14 (phone call): The main clinical efficacy outcome and some secondary outcomes, including clinical progression of signs and symptoms, compliance with the study treatment, EQ-5D-5L instrument, adverse reactions, any complications, reattendance visits, changes in the assigned treatment or concomitant medication, including the use of antibiotics other than the study medication, will be assessed. Patients will be asked to return their diariesDay 28 (phone call): Patients will be contacted for information on the number of reconsultations, complications, and the quality-of-life (EQ-5D-5L) instrument

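### The objective covers 4 weeks of other-antibiotic use, but the outcome stops at 2 weeks and duration ends at discontinuation, so re-treatment is not fully counted in the secondary exposure comparison

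*Protocol article*

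**What the plan says.** All references are to the protocol article.

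- **Objectives.** One secondary objective is: "Evaluate the use of antibiotics other than the study medication and other symptomatic therapies within the first 4 weeks in the 2 groups".
- **Outcomes Collected From the RTI Symptom Diaries.** The matching outcome is "Use of antibiotics other than the study medication and other symptomatic therapies within the first 2 weeks (mean/median". The diary behind it is a 14-day instrument: "Participants will rate symptoms for 14 days and return the diary upon completion (electronically or paper-based". Outcomes 1 to 7 of that list, which include both antibiotic outcomes, are calculated "from day 0 until day 14 or when the participant has scored 0 for every item, whichever comes first".
- **Same section, antibiotic duration.** This is "defined as the number of days until discontinuing treatment in both groups (mean/median". Electronic records are named there as a check on who discontinued and on which day.
- **Outcomes Collected From Electronic Case Report Forms.** The adverse-event item adds "antibiotics changed within the first 14 days". Reattendances, complications and work absence in the same list run to 28 days.
- **Participant Timeline.** The day-7 and day-14 calls list use of antibiotics other than the study drug. The day-28 entry reads: "Patients will be contacted for information on the number of reconsultations, complications, and the quality-of-life (EQ-5D-5L) instrument".

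**The concern.** Two things are wrong on the face of the text. First, the objective and its outcome state different windows. This is not the condensation usual in an article, because both windows are given and they disagree. Second, no listed outcome adds up all the antibiotic a patient takes. Duration closes when treatment is discontinued. A patient who stops early and later resumes the same β-lactam is not using an antibiotic other than the study medication, so the resumed days fit neither outcome.

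The rationale of the strategy is less antibiotic exposure without loss of recovery. The days saved by stopping are counted in full, while days given back through re-treatment are counted in part or not at all. If re-treatment is more frequent after early stopping, the reported saving is larger than the net saving. The Discussion itself names keeping relapse low as the main challenge in deciding when to stop.

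**Working it through.** **Step 1. Windows side by side.**

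| Item | Section | Window |
|---|---|---|
| Objective: other antibiotics, symptomatic therapies | Objectives | 4 weeks |
| Outcome: the same | RTI symptom diaries | 2 weeks |
| Calculation of diary outcomes | RTI symptom diaries | day 14, or earlier once every item scores 0 |
| Antibiotic changes | Electronic case report forms | 14 days |
| Reattendances, complications | Electronic case report forms | 28 days |

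Share of the objective's window with no outcome: (28 − 14) / 28 = 50%. The early cut-off can widen this. As written, a patient who becomes symptom-free on every item, then relapses and is re-treated before day 14, can also fall outside the count.

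**Step 2. Where a second course is recorded.**

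- Different drug, up to day 14: in the separate 2-week outcome, not in duration. A 7-day course starting on day 12 has days 12, 13 and 14 inside the window, 3 of 7.
- Same β-lactam resumed, up to day 14: in neither exposure outcome. The telephone form for patients without a diary asks about antibiotics taken after discontinuation, but no listed outcome uses the answer.
- Any drug, days 15 to 28: in no listed exposure outcome.

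**Step 3. Size.** The documents give no re-treatment rates, so the inputs are assumptions: proportion re-treated in the intervention arm r = 5%, 10% or 15%; in control c = 5%; course length L = 7 or 10 days.

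Days per patient left out of duration: r × L in the intervention arm and c × L in control. Overstatement of the net days saved: (r − c) × L.

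| r | L | Omitted, intervention | Omitted, control | Overstatement |
|---|---|---|---|---|
| 5% | 7 | 0.35 | 0.35 | 0 |
| 5% | 10 | 0.50 | 0.50 | 0 |
| 10% | 7 | 0.70 | 0.35 | 0.35 |
| 10% | 10 | 1.00 | 0.50 | 0.50 |
| 15% | 7 | 1.05 | 0.35 | 0.70 |
| 15% | 10 | 1.50 | 0.50 | 1.00 |

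**Step 4. Sample size, for completeness.** The Sample Size section gives 402 and 474 for the primary endpoint. With 85% in both arms, a 10-point margin, 80% power and one-sided 2.5%, n per arm = 2 × 0.85 × 0.15 × (1.960 + 0.842)² / 0.10² = 200.2, rounded up to 201, or 402 in total. Then 201 / 0.85 = 236.5, rounded up to 237 per arm, or 474. The figure reproduces and does not depend on this point.

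**The case against.** The strongest reply is that most re-treatment that matters is seen somewhere.

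- Under Primary Efficacy Endpoint, a patient who needs further antimicrobial treatment at day 14 is a treatment failure. A relapse treated from day 12 is therefore not hidden.
- A different drug up to day 14 has its own outcome, the diary records daily antibiotic doses, and the no-diary form asks about days actually taken.
- Plans to Promote Participant Retention and Complete Follow-Up refers to medical and shared medication records with little expected loss.
- The duration definition is the same in both arms, so bias needs unequal re-treatment.

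All of this stands, and it limits the point. It does not supply the missing outcome: available records are not a defined endpoint, and the diary section uses records only to check discontinuation.

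A reader might go further in four ways that the documents do not support.

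- *The cost analysis carries the same gap.* Cost-Effectiveness Analyses uses a 28-day within-trial horizon and takes resource use from the day-14 and day-28 calls and medical notes, so later prescriptions may well be costed.
- *Nothing on antibiotics is collected after day 14.* The day-28 list is not exhaustive: Table 3 adds adverse events at that call, and the costing section takes resource use from it.
- *The intervention arm is necessarily flattered, by a particular percentage.* Any such figure rests on one assumed scenario, and equal rates give zero.
- *Work absence is also lost after day 14.* The case-report-form section defines it over 28 days from calls and records. A missing row in Table 3 proves little, since other-antibiotic use has no row either although it is asked on days 7 and 14.

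The contradiction could also be removed by cutting the objective to 2 weeks. That would be consistent, but relapse treatment in days 15 to 28 would still be uncounted while reattendance is followed to day 28.

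**Conclusion.** The point holds as a defect in the secondary antibiotic-exposure comparison. Followed as written, the trial has no outcome that answers its 4-week objective, and a resumed β-lactam or any course in days 15 to 28 enters no listed measure of exposure. Under the assumptions above, the net saving would be overstated by 0 to about 1.0 antibiotic day per patient. The direction favors early stopping only if re-treatment is more frequent in that arm. The textual contradiction is certain; the size is illustrative because the documents give no re-treatment rates. The primary endpoint and the sample size are untouched, and the documents do not show that the cost analysis is affected. It should be corrected, but it does not threaten the main conclusion.

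**What to change.** 1. Reconcile the Objectives and the diary outcome at 28 days for other antibiotics and symptomatic therapies.
2. Define, in both arms, total days on any systemic antibiotic from day 0 to day 28, counting the index course, resumed doses and new courses.
3. Define, in both arms, any new or restarted antibiotic by day 28.
4. State that neither outcome is truncated when all symptom items score 0.
5. Keep days to first discontinuation as a descriptive outcome of the strategy.
6. Add antibiotic and symptomatic-therapy use to the listed content of the existing day-28 call, and check antibiotics against the medication records already in use.

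The cost is outcome wording and a few questions on a call already planned for every patient. The net saving may look slightly smaller. Recruitment was planned to start in October 2025; if it has begun, a dated amendment can make the change, and the medication records can supply antibiotic data for patients already past day 28.
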